### Intervention

At enrolment, households are randomly allocated to either supplementation or not for the duration of pregnancy. Women in the supplementation group receive at home a supply of fortified BEP supplement for daily consumption beginning at 14 gestational weeks until the pregnancy outcome. Both groups also receive (1) recommendation to enrol in ANC at a local health clinic and deliver at a certified birthing facility; (2) nutrition, hygiene, and breastfeeding and infant care counselling; and (3) a clean birthing kit. In pregnancy, women in both groups are provided iron–folic acid tablets and albendazole, if not provided via ANC at their health facility. At the birth visit, households where a woman reports at least one live birth are randomly allocated to either supplementation or not for the postpartum period until the infant is 6 months old. Counselling for exclusive breastfeeding is provided in the postpartum period but iron–folic acid tablets are not provided as per the policy in Nepal.

#### Composition of fortified BEP supplement

The fortified BEP supplement is a ready-to-eat snack in the form of lipid-based peanut paste packaged in individual sachets (72 g). The supplement was designed to meet the expert consensus specifications of a nutritious food supplement for pregnant and lactating women.^16^ Each sachet is a daily portion that provides calories (~400 kcal), protein (~14 g) and multiple micronutrients at the estimated average requirement for pregnancy. The product is made by Nutriset (France), as a specially manufactured version of their product known as ‘Plumpy’Mum’. We previously conducted two formative research studies to evaluate the acceptability of and adherence to various flavours of the BEP product in this community.^23 24^ Due to unavailability of raw materials, Nutriset produced three variations of Plumpy’Mum for use in our study, each with different combinations of ingredients selected to produce a product with a similar nutritional composition. The changes to the original ingredients were to remove the soy isolate (first change) and soy flour (second change), which resulted in minor changes in energy, protein and micronutrient concentrations, deemed inconsequential from a nutrition perspective. The specific ingredients and nutritional composition of each variation are provided in the online supplemental table 2.

### Outcomes

The study has two primary outcomes, one each for the pregnancy and postpartum/postnatal periods, respectively. The primary outcome for the pregnancy period is incidence of SGA among live born infants with birth weight measured within 72 hours of delivery. SGA is defined as weight measured within <72 hours of delivery <10th centile of the INTERGROWTH-21st reference standard by gestational age and sex.^25^ We assessed gestational age using first or second trimester ultrasound examination prior to 24 gestational weeks. The primary outcome for the postpartum/postnatal period is mean LAZ at 6 months using the international WHO international growth reference.^26^ Secondary outcomes are listed in table 1.

**Table 1 T1:** MINT Study primary and secondary outcomes

Primary outcomes	
Small-for-gestational-age (10th centile)	Proportion of infants with birth weight <10th centile of INTERGROWTH-21st reference standard by gestational age and sex for infants measured <72 hours after delivery
Length-for-age z-score (LAZ)	Mean infant length-for-age z-score at 6 months of age using the WHO international growth reference
**Secondary outcomes**	
Newborn	
Small-for-gestational-age (3rd centile)	Proportion of infants with birth weight <3rd centile of INTERGROWTH-21st reference standard by gestational age and sex for infants measured <72 hours after delivery
Large-for-gestational-age (90th centile)	Proportion of infants with birth weight >90th centile of INTERGROWTH-21st reference standard by gestational age and sex for infants measured <72 hours after delivery
Short-for-gestational-age (10th centile)	Proportion of infants with birth length <10th centile of INTERGROWTH-21st reference standard by gestational age and sex for infants measured <72 hours after delivery
Short-for-gestational-age (3rd centile)	Proportion of infants with birth length <3rd centile of INTERGROWTH-21st reference standard by gestational age and sex for infants measured <72 hours after delivery
Birth weight	Mean infant birth weight
Birth length	Mean infant birth length
Head circumference	Mean infant head circumference
Arm circumference	Mean infant mid-upper arm circumference
Low birth weight	Proportion of infants with birth weight <2500 g for infants measured <72 hours after delivery
Gestational age	Mean infant gestational age at delivery
Preterm birth (<37 weeks)	Proportion of pregnancies that are <37 gestational weeks using the INTERGROWTH-21st standards for 1st and 2nd trimester ultrasound dating
Very, extremely preterm (<34, <32, <28 weeks)	Proportion of pregnancies that are <34, <32, <28 gestational weeks using the INTERGROWTH-21st standards for 1st and 2nd trimester ultrasound dating
Stillbirth	Proportion of pregnancies resulting in stillbirth, defined as fetal death ≥28 gestational weeks, using the INTERGROWTH-21st standards for 1st and 2nd trimester ultrasound dating
Weight-for-length z-score at 6 months of age	Mean infant weight-for-length z-score at 6 months of age using the WHO international growth reference
Weight-for-age z-score at 6 months of age	Mean infant weight-for-age z-score at 6 months of age using the WHO international growth reference
Stunting	Proportion of infants with <−2 length-for-age z-score at 6 months of age using the WHO international growth reference
Wasting	Proportion of infants with <−2 weight-for-length z-score at 6 months of age using the WHO international growth reference
Underweight	Proportion of infants with <−2 weight-for-age z-score at 6 months of age using the WHO international growth reference
Developmental scales	Bayley Scales of Infant and Toddler Development 4 assessment at 6 months
Gross motor milestones	WHO 6 gross motor milestones at 6 months
Gut microbiome	Gut microbiome diversity and stool metabolomics at 3 and 6 months
Maternal	
Gestational weight gain	Mean maternal weight gain from enrolment to late pregnancy visits
Net gestational weight gain	Mean maternal weight gain from enrolment to maternal birth assessment visit (after delivery)
Inadequate maternal gestational weight gain	Proportion of women with inadequate rate of gestational weight gain from enrolment to late pregnancy visit using the INTERGROWTH-21st reference for normal body mass index (BMI) and IOM reference for low and high BMI
Inadequate maternal net gestational weight gain	Proportion of women with inadequate rate of gestational weight gain from enrolment to maternal birth assessment visit using the INTERGROWTH-21st reference for normal BMI and IOM reference for low and high BMI
Mid-upper arm circumference	Mean change in mid-upper arm circumference from enrolment to late pregnancy visits
Anaemia	Proportion of women who are anaemic (haemoglobin <110 g/L) in late pregnancy
Weight at 6 months post partum	Mean maternal weight at 6 months post partum
Maternal dietary intake	Mean maternal dietary intake score in late pregnancy and 3 months post partum
Minimum maternal dietary intake	Proportion of women meeting the minimum dietary intake score in late pregnancy and 3 months post partum
Gut microbiome	Gut microbiome diversity and stool metabolomics during pregnancy
Metabolites	Metabolites in the blood during pregnancy

IOM, American Institute of Medicine; MINT, Maternal Infant Nutrition Trial.

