#### Late pregnancy visit

FIs conduct a late pregnancy visit between 32 and 34 gestational weeks to collect data on maternal anthropometry (same measures as enrolment), maternal morbidities, tobacco/alcohol use, ANC utilisation, delivery planning, diet diversity, household food security and depression (using a version of the Edinburgh Postnatal Depression Scale validated in Nepali).^30^

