#### Birth assessment visit

FIs aim to visit each woman within 72 hours of delivery to collect information about the birth and delivery process, early breastfeeding and feeding behaviours, and newborn care practices. Infant weight (g), length (cm), head circumference (cm) and temperature (°F) are measured. Weight is measured with digital scales (Tanita BD-585), length with Shorr-type boards and MUAC with non-stretchable insertion tape. Non-digital measures are taken in triplicate and the median is used for analysis.

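### Net weight gain, taken from a weight after delivery, is classed as inadequate against the same rate references used for women who are still pregnant

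*Protocol article*

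**What the plan says.** The maternal part of Table 1 (Outcomes) lists two kinds of weight gain, each as a mean and as a proportion with an inadequate rate.

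- **In-pregnancy gain** runs to the late pregnancy visit. The proportion row reads "inadequate rate of gestational weight gain from enrolment to late pregnancy visit using the INTERGROWTH-21st reference for normal body mass index (BMI"). Women of low or high BMI are judged by the IOM reference instead. On timing, the section on that visit says "FIs conduct a late pregnancy visit between 32 and 34 gestational weeks".
- **Net gain** runs to the birth assessment visit. The mean row reads "Mean maternal weight gain from enrolment to maternal birth assessment visit (after delivery"). The proportion row reads "Proportion of women with inadequate rate of gestational weight gain from enrolment to maternal birth assessment visit using the INTERGROWTH-21st reference". As in the other proportion row, this reference covers normal BMI only, and the IOM one covers the remaining women. On timing, the section on that visit says "FIs aim to visit each woman within 72 hours of delivery".

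The article therefore separates the two quantities and then names the same pair of references for both. It mentions no allowance for what leaves the scale at delivery.

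**The concern.** The two end weights differ by the infant, the placenta and the fluid. If a rate threshold marks inadequate gain in a woman who is still pregnant, applying it unchanged after delivery sets a much harder test. A woman whose gain in pregnancy was above the threshold by less than the delivery loss per week moves into the inadequate class merely because she has delivered.

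At stake is the meaning of one secondary proportion. The reported prevalence of inadequate net gain would partly reflect delivery and not maternal nutrition. It would also not be comparable with the in-pregnancy proportion beside it, although the shared label and references invite that comparison. The Dissemination plan foresees sharing data for meta-analyses, so the figure could travel beyond this trial.

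**Working it through.** The article gives no expected proportion, gain distribution or cut-off for either inadequate-gain row, so there is no figure of the plan's own to reproduce. The check covers the direction, the size of the shift in weekly rate, and what that shift does to a comparison of arms.

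**Direction.** Let *r* be the weekly gain up to delivery, *d* the weight leaving at delivery divided by the weeks from enrolment to birth, and *c* the threshold. The net rate is *r* − *d*, and it is classed as inadequate when *r* − *d* < *c*, that is, when *r* < *c* + *d*. Since *d* > 0, P(*r* < *c* + *d*) cannot be smaller than P(*r* < *c*). The proportion can only go up, in either arm.

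**A floor for the shift.** Study setting gives 30.1% low birth weight in the earlier trial in this area, so about 69.9% of infants weighed at least 2.5 kg. Spread over 40 weeks, taken here as longer than any enrolment-to-birth interval, the infant alone accounts for at least 2.5 / 40 = 0.06 kg/week for those mothers.

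**A working range.** Inputs: 30.1% LBW (document); birth weight SD 430 g, placenta and fluid 1.0 to 1.5 kg, and an interval of 23 to 29 weeks (all assumed).

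- Mean birth weight: 2500 + 0.52 × 430 = 2724 g, about 2.72 kg.
- Low end: (2.72 + 1.0) / 29 = 0.128, about 0.13 kg/week.
- High end: (2.72 + 1.5) / 23 = 0.183, about 0.18 kg/week.

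With wider assumptions (2.5 to 6 kg leaving, over 16 to 30 weeks) the range is 2.5 / 30 = 0.08 to 6 / 16 = 0.38 kg/week.

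**Effect on the group difference.** For illustration only, take weekly rates as normal with SD 0.12 and a supplement effect of 0.02 kg/week, and vary the proportion of controls who would be inadequate without the shift. For a starting proportion *p*, the control proportion after a shift *d* is Φ(Φ⁻¹(*p*) + *d*/0.12). The supplemented proportion uses *d* − 0.02 in place of *d*.

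| Control proportion, no shift | Difference, no shift (points) | Difference, shift 0.13 | Difference, shift 0.18 |
|---|---|---|---|
| 10% | 2.6 | 6.4 | 6.6 |
| 20% | 4.3 | 6.6 | 5.6 |
| 30% | 5.5 | 5.9 | 4.5 |
| 50% | 6.6 | 4.0 | 2.4 |
| 70% | 6.0 | 2.1 | 1.0 |

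From 50%, the control proportion itself becomes 86% (shift 0.13) or 93% (shift 0.18). From 10%, it becomes 42% or 59%. The inflation is large in every row, but the difference between arms may grow or shrink according to the starting point, which the article does not give. In the 50% row, with 774 women per arm (1548 / 2), the standardised difference goes from about 2.6 to 2.2 or 1.8, a smaller loss than the fall in points suggests.

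**The case against.** **The references are not in the article, and scoring details may sit in the analysis plan.** This is partly right. That the references describe gain in women still pregnant is inferred from their use at the late pregnancy visit. But the inference is not essential: one unadjusted threshold cannot suit both weights, whichever it was built for. Nor is the point an omission. The article names the reference for this row. An adjustment specified elsewhere would answer the concern, but nothing shown here points to one.

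**The shift is nearly the same in both arms, so it does not by itself bias the comparison.** This stands. The damage is mainly to the label and to the absolute prevalence.

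**The trial's stated interest in inadequate weight gain is already served.** This also stands. The summary box and the Discussion speak of inadequate gestational weight gain, which has its own row measured before delivery.

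**Stronger readings a reader might infer.** One is that the proportion approaches 100% and the contrast between arms is lost. That needs a threshold at or above the average gain, and the document gives neither quantity. From a 10% start the illustrative difference rises.

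Another is that Table 1 makes the same kind of error for preterm birth, since "Proportion of pregnancies that are <37 gestational weeks using the INTERGROWTH-21st standards for 1st and 2nd trimester ultrasound dating" has no lower gestational limit and would, taken literally, count miscarriages. The document does not support this. The rows are labelled as preterm birth and as very or extremely preterm, they stand under the newborn heading, and no text counts early losses. The denominator and lower limit could be stated more clearly, but a condensed article may leave them to the full protocol. Restricting to live births would be a debatable convention, because it conditions on an event after randomisation.

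**Conclusion.** The concern holds for one row of Table 1: the proportion with inadequate net gestational weight gain. As written, the rule over-counts inadequate net gain in both arms. The weekly rate is lowered by about 0.13 to 0.18 kg under the assumed birth weight SD, placenta and fluid weight and interval. The documents' own low-birth-weight figure supports a floor of about 0.06 kg/week for most mothers. The direction does not depend on these assumptions. The size of the inflation and the effect on the contrast between arms do depend on a gain distribution and cut-offs that the document does not give, and no claim is made about them.

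The scope is narrow. Mean net gain, the in-pregnancy rows, both primary outcomes and the sample size are untouched. The change is still worth making, because the mismatch is visible in the table itself and cheap to remove.

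**What to change.** Preferred: delete the inadequate-net-gain proportion, analyse net gain as a mean in kg, and use the INTERGROWTH-21st and IOM references only for weight at the late pregnancy visit. The mean is already a Table 1 outcome, so no new data or analysis are needed.

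Alternative: keep the row, but name a reference meant for weight after delivery, or pre-specify how the delivered weight is allowed for before the comparison with the reference.

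The cost is an edit to one row of Table 1 and the matching text of the analysis plan. One secondary proportion is lost or redefined. The change should be dated and made before outcome data are compared by arm.

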### Sample size

With a sample size of 1548 woman/infant pairs visited within <72 hours of delivery, we will be able to detect a 17.5% reduction in SGA with 80% power and a 20.2% reduction with 90% power assuming a type 1 error of 5% (two-sided). Since we are assuming no interaction between the marginal effects, this sample size will allow us to detect a difference in infant LAZ at 6 months after delivery of 0.16 z-scores with 80% power and 0.18 z-scores with 90% power. The MINT Study is designed to enrol approximately 1800–2000 women over a period of 20 months (split into two 6-month enrolment periods). This will yield the required sample of 1548 woman/infant pairs visited within 72 hours of delivery, after a reduction of 14% due to fetal death and loss to follow-up in pregnancy.

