### Study setting

The MINT Study is conducted in Sarlahi District, Madhesh Province, in the Terai region (low-lying plains) of Nepal by the NNIPS research team. The NNIPS field research site, established in 1989 and covering approximately one-third of the district, currently operates as a joint undertaking between the Department of International Health, Johns Hopkins Bloomberg School of Public Health, and the non-profit organisation, Nepal Netra Jyoti Sangh, under a memorandum of agreement with the Social Welfare Council, Government of Nepal. Nepal’s Terai region has high rates of maternal undernutrition, neonatal mortality, adverse pregnancy outcomes and inadequate infant growth, and is representative of rural, low-income settings in much of South Asia.^21^ Over half (56.9%) of households in Nepal’s Madhesh Province faced food insecurity with 10% being severely food insecure, according to the Nepal Demographic and Health Survey 2016.^21^ Of children under 5 years old, 29.3% were stunted and 10.1% were wasted in Madhesh Province in 2022.^22^ Data from our most recent trial in the NNIPS study area, which had over 31 000 live births (2010–2017), reported neonatal mortality and stillbirth rates of approximately 32 per 1000 live births and 29 per 1000 births, respectively (unpublished). In that trial, the proportion of adverse pregnancy outcomes were: preterm birth 14.9%, SGA 48.5% and LBW 30.1% (unpublished). Nearly one-third of women in their first trimester of pregnancy were underweight (29.5%) (body mass index (BMI) <18.5 kg/m^2^) and the same proportion (29.5%) had a height less than 145 cm (unpublished). Over one-third of infants (35%) are breastfed within an hour of birth and 95% within 24 hours in our trial population (unpublished).

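### The detectable LAZ differences at 6 months use the birth-visit sample of 1548 unchanged, with no allowance for infant death or loss after birth

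*Protocol article*

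**What the plan says.** All references are to the protocol article.

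- **Sample size.** The SGA calculation starts "With a sample size of 1548 woman/infant pairs visited within <72 hours of delivery", with the condition "assuming a type 1 error of 5% (two-sided"), and claims power to "detect a 17.5% reduction in SGA with 80% power and a 20.2% reduction with 90% power".
- **Same section, LAZ.** The next sentence carries the number over: "this sample size will allow us to detect a difference in infant LAZ at 6 months after delivery of 0.16 z-scores with 80% power". The corresponding LAZ figure for 90% is 0.18. No SD for LAZ and no control SGA rate are given.
- **Same section, enrolment.** The plan is to enrol about 1800–2000 women and to reach 1548 pairs "after a reduction of 14% due to fetal death and loss to follow-up in pregnancy". No other reduction is named.
- **Statistical analysis, Primary aim 2.** The LAZ analysis is restricted to children whose length was taken at 6 months.
- **Study setting.** The previous trial at the site had "neonatal mortality and stillbirth rates of approximately 32 per 1000 live births and 29 per 1000 births" respectively, and an SGA proportion of 48.5%.
- **Birth assessment visit.** "FIs aim to visit each woman within 72 hours of delivery"; no expected success rate is given.
- **Study population and recruitment.** 1944 women had been enrolled by August 2023.

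**The concern.** The number that supports the LAZ statement is a count of pairs at birth, whereas the LAZ endpoint is measured half a year later. Using the same number for both means that no infant dies, moves away or misses the 6-month visit. The article's own neonatal mortality figure rules that out. If the LAZ power is overstated, a null or imprecise lactation result could later be read as stronger evidence of no effect than the analysed sample supports. LAZ is one of the two primary outcomes, so its stated power should rest on the infants who will be analysed.

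**Working it through.** **Inputs from the article:** enrolment 1800 (lower end of 1800–2000) and 1944 (actual); 14% reduction; two-sided 5% error; LAZ 0.16 at 80% and 0.18 at 90% power; neonatal mortality 32 per 1000; site SGA 48.5%.

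**Assumptions:** 1:1 allocation, so each factorial margin compares N/2 with N/2; no interaction, as the article itself assumes; the SD of LAZ and the control SGA rate are back-solved because neither is stated; postnatal loss of 10–20% is an illustrative range, because the article gives none.

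**1. Where 1548 comes from.** 1800 × (1 − 0.14) = 1548 exactly. At 1800 enrolled, the pregnancy losses use up the whole margin.

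**2. Reproducing the LAZ figures.** Detectable difference = (1.96 + z_power) × SD × √(4/N), with z = 0.842 for 80% and 1.282 for 90%. At N = 1548, √(4/N) = 0.0508.
- SD implied by 0.16 at 80%: 0.16 / (2.802 × 0.0508) = 1.12.
- SD implied by 0.18 at 90%: 0.18 / (3.242 × 0.0508) = 1.09.
- A single SD of 1.1 gives 0.157 and 0.181, which round to the stated 0.16 and 0.18.

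So the stated pair is what one gets from all 1548, without postnatal loss, if the SD is about 1.1.

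**3. How much slack there is.** With SD 1.1, 0.16 at 80% power needs about 1484 infants, which is 4% below 1548. For 0.18 at 90%, about 1570 are needed, so there is no slack beyond rounding. Neonatal deaths alone leave 1548 × 0.968 = 1498, which gives 0.159 and 0.184. These still round to the stated figures.

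**4. Adding postnatal loss (SD 1.1).**

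| Enrolled | After 14% | Further loss | N at 6 months | 80% power | 90% power | Power at 0.16 |
|---|---|---|---|---|---|---|
| 1800 | 1548 | 0% | 1548 | 0.157 | 0.181 | 82% |
| 1800 | 1548 | 10% | 1393 | 0.165 | 0.191 | 78% |
| 1800 | 1548 | 15% | 1316 | 0.170 | 0.197 | 75% |
| 1800 | 1548 | 20% | 1238 | 0.175 | 0.203 | 73% |
| 1944 | 1672 | 10% | 1505 | 0.159 | 0.184 | 81% |
| 1944 | 1672 | 15% | 1421 | 0.164 | 0.189 | 78% |
| 1944 | 1672 | 20% | 1337 | 0.169 | 0.195 | 76% |

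Further loss that can be absorbed before falling below 1548: 1 − 1548/1672 = 7.4% at 1944 enrolled, and 1 − 1548/1720 = 10.0% at 2000.

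**5. SGA, for comparison.** With the usual two-proportion formula (pooled variance under the null, 774 per group), a control rate of 39% reproduces the stated figures: 17.5% at 80% and 20.1% at 90%. At that rate, if 10% or 20% of the 1548 were not weighed in time, the 80% figure would become 18.4% or 19.5%. At the site's 48.5%, a 17.5% reduction has 92% power with 1548, 89% with 1393 and 85% with 1238, and needs only about 1074 pairs for 80%.

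**The case against.** Four arguments on the other side deserve weight.

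**The SD is unstated.** With SD 1.0, the stated 0.16 and 0.18 correspond to about 1226–1297 infants, a postnatal loss of 16–21%; with SD 1.05, to about 1352–1430, a loss of 8–13%. An allowance could therefore be built in silently. This cannot be excluded, but the text attributes the LAZ figures to the same sample size and mentions no postnatal loss, so 1548 with SD near 1.1 is the plainer reading. The uncertainty about the size of the effect stands.

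**Enrolment was not fixed at 1800.** The plan gives 1800–2000, and 1944 were enrolled. That absorbs about 7–10% further loss. This stands, and it removes most of the practical shortfall unless postnatal loss is well above 10%. The article does not present the extra enrolment as an allowance for postnatal loss, however.

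**The loss rates are assumed.** Correct: the only figure in the article is neonatal mortality, which by itself does not move the rounded LAZ figures.

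**SGA.** A reader might infer that the SGA figures are too favourable as well, because the birth visit within 72 hours is only an aim. The article does not support that. It defines the 1548 as pairs already seen within the window, which is the right analysis set. The gap is only that late visits are not named among the reasons for the 14%. The figures would be too favourable only if the design rate was near 39% and late visits come on top of the 14%. At the only SGA rate given for the site, 48.5%, they are conservative.

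**Conclusion.** The mismatch is real. The LAZ detectable differences are stated for a birth-visit count, while the analysis takes infants measured at 6 months, and no loss between the two is allowed for. The size is small: about 0.005–0.015 z-scores at 80% power for 1800 enrolled, and less than 0.01 for 1944 enrolled, across an assumed 10–20% postnatal loss. It rests on an inferred SD of about 1.1 and on those assumed losses. At 1944 enrolled with about 10% loss, the stated 0.16 and 0.18 survive rounding. The severity is minor: neither the design nor the analysis is undermined, and nothing is shown against the SGA figures.

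**What to change.** In the sample size section:

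1. Give LAZ its own analysed N: actual enrolment × 0.86 × expected retention to the 6-month measurement.
2. State the SD assumed for LAZ and restate the 80% and 90% detectable differences from that N. If SD 1.1 is right, 1944 enrolled with 15–20% loss gives about 0.164–0.169 and 0.189–0.195.
3. If a postnatal allowance is already contained in the stated figures, say so and give the number of infants behind it.
4. State the control SGA rate used, and whether the 14% includes births not reached within 72 hours.

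The cost is an edit to one paragraph and possibly slightly less favourable LAZ figures. No extra enrolment and no change to the analysis is needed.
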